### Sample size

2.4

The frequency of acute exacerbations is the primary outcome. According to the data in previous studies, the annual frequency of acute exacerbations in the control group was 1.08 episodes (27), and the experimental group is expected to have a 40% reduction (28), i.e., 0.648 episodes. The test level (*α*) and power (1 − *β*) of the hypothesis test were set at 0.05 and 0.9, and the sample size ratio of the experimental group and control group was 1:1. The estimated sample size for each group was 359 participants using PASS software. After accounting for a 15% dropout rate, the required sample size per group was adjusted to 423 participants. Due to the centralized blocked randomization with block sizes of 4, the sample size per group was adjusted to 424 participants. A total of 848 subjects will be enrolled in this trial.

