### Statistical analysis

2.9

SPSS software (Version 25.0) will be used for statistical analysis in this study. The study data will be analyzed according to the ITT principle, where all randomized participants will be included in the analysis according to their original group assignment, regardless of protocol deviations or different follow-up durations. For participants with varying follow-up durations, mixed-effects models for repeated measures will incorporate time as a covariate to utilize available data. Missing data will be handled using mixed-effects models for repeated measures as the primary method, with multiple imputation conducted as a sensitivity analysis. Continuous variables will be expressed as either mean ± standard deviation (assuming normal distribution) or median (interquartile range) (non-normal distribution). For the primary outcome, Poisson regression or negative binomial regression will be used based on overdispersion tests (assuming Poisson or negative binomial distribution). For secondary outcomes: count data will use the same methods as the primary outcome; binary data will use logistic regression (assuming binomial distribution); continuous data will use repeated-measures analysis of variance (for normal distribution) or Friedman test (for non-normal distribution). Mauchly’s test will first be applied to assess sphericity for repeated measures. If the assumption is violated (*p* < 0.05), the Greenhouse–Geisser correction will be implemented. Pairwise comparisons within groups will use the Bonferroni method, between groups the LSD-*t* test (equal variances) or Tamhane’s T2 method (unequal variances). Categorical variables will be presented as frequency (%) and compared using the chi-square test (large samples) or Fisher’s exact test (small samples with <5 expected counts). Outliers will be identified using box plots (values beyond 1.5 × interquartile range), verified for data accuracy, and retained in the primary analysis; sensitivity analyses excluding outliers will be conducted. For all statistical tests, both *p*-values and 95% confidence intervals will be reported. A hierarchical testing strategy will be used for multiple comparisons: the primary outcome will be tested first; if significant, secondary outcomes will be tested with Bonferroni correction to control type I error, aligning with the outcome hierarchy. A *p*-value <0.05 is considered statistically significant.

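### Section 2.9 names two incompatible main analyses for the continuous secondary outcomes: a mixed model that keeps incomplete patients, and repeated-measures ANOVA or Friedman tests that drop them

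*Protocol article*

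**What the plan says.** All the conflicting statements are in section 2.9 (Statistical analysis) of the protocol article.

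- **Population:** "all randomized participants will be included in the analysis according to their original group assignment".
- **Missing data:** "Missing data will be handled using mixed-effects models for repeated measures as the primary method", "with multiple imputation conducted as a sensitivity analysis".
- **Unequal follow-up:** "mixed-effects models for repeated measures will incorporate time as a covariate to utilize available data".
- **Test for continuous secondary outcomes:** "continuous data will use repeated-measures analysis of variance (for normal distribution) or Friedman test (for non-normal distribution".
- **Sphericity:** for Mauchly's procedure, "test will first be applied to assess sphericity for repeated measures", followed by the Greenhouse-Geisser correction if sphericity is rejected.

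Section 2.3.4 repeats the mixed-model approach for patients completely lost to follow-up. Section 2.7.2 and Table 2 schedule the continuous outcomes at baseline and weeks 13, 26, 39 and 52, which makes five measurements. Section 2.4 sets the expected loss: "After accounting for a 15% dropout rate".

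**The concern.** A likelihood-based mixed model and a classical repeated-measures ANOVA are not two names for one analysis. The mixed model uses whatever visits a patient has. The ANOVA, and the Friedman test offered as its non-normal alternative, need a full row of measurements for each patient. A patient seen at four of five visits contributes four values to the first and nothing to the second.

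Two things are at stake. First, if the ANOVA or Friedman wording is applied, the result is an analysis of patients with complete data, and calling it intention-to-treat would be wrong. Second, each continuous secondary outcome has two candidate p-values from different sets of patients. Section 2.9 tests the secondary outcomes with Bonferroni correction once the primary outcome succeeds, and that error control presupposes one designated test per outcome.

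**Working it through.** **1. The plan's own dropout figure.** Section 2.4 starts from 359 per group and allows 15% dropout: 359 / (1 − 0.15) = 422.4, rounded up to 423. The next multiple of the block size 4 is 424, and 2 × 424 = 848. The step reproduces. The 15% is thus a planning allowance used to inflate the sample size.

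**2. Can the two instructions be read as one?**

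| Question | Mixed model (2.9, 2.3.4) | ANOVA or Friedman (2.9) |
|---|---|---|
| Patient with a missing visit | Kept, using the observed visits | Dropped |
| Within-patient correlation | Modelled through a covariance structure | Sphericity in the ANOVA, checked by Mauchly, corrected by Greenhouse-Geisser |
| All randomised patients analysed? | All with at least one measurement of the outcome | Only those with all five |

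Mauchly's test and the Greenhouse-Geisser correction belong to classical ANOVA and have no role in a mixed model, so ANOVA is not loose wording for the mixed model here. Imputing before the ANOVA would restore complete rows, but section 2.9 confines imputation to sensitivity analysis.

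**3. Patients excluded under the ANOVA or Friedman wording.** Let m be the chance that a patient who does not drop out misses any one of the four post-baseline visits. The expected number of complete rows is 848 × 0.85 × (1 − m)^4. Values of m above 0 are assumptions; the documents give none.

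| m | Complete rows | Excluded |
|---|---|---|
| 0 | 848 × 0.850 = 721 | 127 (15%) |
| 0.02 | 848 × 0.784 = 665 | 183 (22%) |
| 0.05 | 848 × 0.692 = 587 | 261 (31%) |

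**4. Measurements discarded.** Assume the 15% leave evenly over the four intervals and no other visit is missed. Observed patient-visits are 848 × (5 − 0.15 × (1 + 2 + 3 + 4)/4) = 848 × 4.625 = 3,922. Complete rows hold 848 × 0.85 × 5 = 3,604. The difference, 318 observed measurements per outcome, is used by the mixed model and thrown away by the ANOVA.

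**5. Effect on the arm difference.** This depends on how dropout relates to outcome in each arm, which the documents cannot tell us. Simulations with 424 per arm show the range.

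- *Same dropout mechanism in both arms* (correlation 0.7 between adjacent visits, decaying with distance; about 16% dropout depending on the previous value; true week-52 difference 0.200 SD). Complete cases shift the control-arm week-52 mean by 0.08 SD, but the arm difference is 0.194. Likelihood estimation gives 0.200.
- *Dropout tied to the previous value in one arm only* (15% dropout). The complete-case week-52 difference is biased by about 0.065 to 0.10 SD, depending on how strong that tie is assumed to be. A week-52 comparison at the nominal 5% level then rejects a true null in 13 to 27% of trials. Likelihood estimation shows no bias.

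The simulated data were missing at random by construction. The good performance of likelihood estimation is conditional on that and says nothing about data missing for unobserved reasons.

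**The case against.** The best defence is that the mixed model already governs whenever data are missing. Section 2.9 names it for missing data and for unequal follow-up, section 2.3.4 repeats it, and a statistical analysis plan that is not shown may settle the order. This stands in part: the text does not commit the trial to a completers' analysis, and a reader who infers that it does goes beyond the documents. The conflict remains, though. The rule 'mixed model if data are missing, ANOVA otherwise' is nowhere written, and with 15% dropout expected it would leave the ANOVA instructions with almost nothing to do.

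A second defence concerns size. A reader might take 127 as the minimum number lost. The documents do not support that: 15% is a planning allowance, section 2.3.4 keeps following patients who stop treatment, and section 2.8.2 adds monthly calls and quarterly home visits. The real share with incomplete data could be lower. It could also be higher, because dropout is not the only way to miss one visit of five.

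A third defence concerns bias. A reader might infer from the one-arm simulations that false positives are to be expected. That pattern is an assumed adverse case, nothing in the documents points to it in a double-blind trial, the rates ignore the planned Bonferroni correction, and the week-52 contrast is not itself the ANOVA test. With similar dropout in both arms, the difference barely moves. This objection stands: bias is possible, not predicted.

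**Conclusion.** The contradiction is real and rests on the text alone: section 2.9 designates two main analyses of the continuous secondary outcomes that use different patients. The stated intention-to-treat principle is compatible with only one of them.

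The consequences are conditional. If the ANOVA or Friedman wording is followed and 15% of patients have incomplete data, about 127 of 848 are excluded; the range of 183 to 261 further assumes that 2 to 5% of visits are missed. Bias in the arm difference requires outcome-related dropout that differs between arms.

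It would also be wrong to infer that the trial's main conclusion is at risk. The primary outcome is a count analysed by Poisson or negative binomial regression, and the secondary outcomes are tested only if it succeeds. This should be fixed before database lock, but it does not threaten the primary result.

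**What to change.** State in section 2.9, and in the analysis plan, that the sole main analysis of lung function, 6MWD, symptom scores, CAT and SF-36 is a mixed model for repeated measures with arm, visit and arm-by-visit terms and a prespecified covariance structure (unstructured, for example). Delete repeated-measures ANOVA, the Friedman test, Mauchly's test and the Greenhouse-Geisser correction, or label them together as a completers' sensitivity analysis. Friedman has to be included: if it stays as the main test for non-normal outcomes, the same conflict survives there. Multiple imputation can remain a sensitivity analysis as planned.

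The cost is a change of wording, since the mixed model is already in the plan and no new data are needed. There is time: the Trial status section puts the end of data collection at 31 December 2026 and the start of analysis at 1 March 2027. The change should be dated and made while the data are still blinded.

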#### Withdrawal/termination criteria

2.3.4

Patients with any of the following conditions will be withdrawn or terminated from the intervention, but will continue to be followed for outcome assessment and included in the Intention-To-Treat (ITT) analysis according to their original group assignment, unless truly lost to follow-up:

(1) Patients who experience serious adverse reactions or allergies after taking BFYS granules. In this study, serious adverse reactions include events that result in death, are life-threatening, require hospitalization or prolongation of existing hospitalization, or lead to persistent or significant disability/incapacity.(2) Patients who have disease progression, such as uncontrolled AECOPD or concurrent severe illnesses (e.g., acute cardiovascular events).(3) Patients who commit serious protocol violations, including unauthorized use of prohibited medications, or ≥4 consecutive weeks of non-adherence to study drugs.(4) Patients who show poor treatment response, with worsened symptoms or a ≥ 10% decline in FEV1 compared to baseline at any 13-week assessment visit.(5) Patients who enroll in other clinical studies.(6) Patients who voluntarily request to withdraw from the intervention.

Complete loss to follow-up refers to patients with objective inability to follow up due to severe physical impairment, geographical relocation, or confirmed cognitive decline, resulting in the inability to conduct any outcome assessments. These patients will be withdrawn from the study, and their data will be handled according to the ITT principle with missing data addressed using mixed-effects models for repeated measures and multiple imputation in sensitivity analyses.

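### The only sensitivity analysis named for missing data is multiple imputation, which in its standard form shares the mixed model's missing-at-random assumption and does not test departures from it

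*Protocol article*

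**What the plan says.** Section 2.9 (Statistical analysis) of the protocol article states: "Missing data will be handled using mixed-effects models for repeated measures as the primary method", "with multiple imputation conducted as a sensitivity analysis". Section 2.3.4 (Withdrawal/termination criteria) applies the same pair to patients who are completely lost: "missing data addressed using mixed-effects models for repeated measures and multiple imputation in sensitivity analyses". It attributes complete loss to serious physical decline, moving away, or cognitive deterioration. Patients who only stop the intervention remain in follow-up and in the intention-to-treat analysis.

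The one other sensitivity analysis named in Section 2.9, "sensitivity analyses excluding outliers will be conducted", concerns extreme values and not missing ones. The exacerbation count has its own model: "For the primary outcome, Poisson regression or negative binomial regression will be used based on overdispersion tests". Section 2.4 (Sample size) gives the only figure for attrition: "After accounting for a 15% dropout rate, the required sample size per group was adjusted to 423 participants".

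The article does not state a missingness assumption, an imputation model, or a delta or reference-based rule.

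**The concern.** A sensitivity analysis for missing data is useful when it changes the assumption that the data cannot check. A likelihood-based mixed model is valid if data are missing at random, meaning that after allowing for what was observed, lost patients would have gone on like similar patients in their own arm. Multiple imputation run in the standard way assumes the same. The two will usually agree whether or not the assumption is true.

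The assumption is open to doubt here. Because patients who stop treatment are still followed, the outcomes that stay missing come mainly from the completely lost group, and two of the three reasons given for that loss concern health. Lost BFYS patients presumably also stop taking the granules. Crediting them with the on-trial rate of their own arm may then favour BFYS.

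At stake is the reading of a modest positive result, which could be reported as robust on the strength of a check that did not stress it.

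**Working it through.** **Inputs.** From Section 2.4: control rate 1.08 per year, experimental rate 0.648 (rate ratio 0.60), alpha 0.05 (taken as two-sided), power 0.90, 359 per group before dropout, 15% dropout. Not given: the dispersion k, so it is an assumption with a range.

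**The plan's own figures.** 359/(1 − 0.15) = 422.4, so 423, and 424 for blocks of 4. This reproduces. Fifteen per cent of 424 is about 64 patients per arm.

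The 359 does not follow from the stated inputs alone. With n = (1.960 + 1.282)² × (1/1.08 + 1/0.648 + 2k) / (ln 0.60)²:
- k = 0 (Poisson): 10.507 × 2.469 / 0.2609 = 99.4, so 100 per group
- k = 0.5: 140; k = 1: 180; k = 2: 261
- k = 3.22: 10.507 × (2.469 + 6.44) / 0.2609 = 358.7, so 359

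The back-solved 3.22 is used as the top of the range and 0.5 as the bottom.

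**Scenario.** All 15% are lost at the start, and the lost BFYS patients have the control rate:
- Shifted ratio = 0.85 × RR + 0.15 × 1
- SE(log RR) = √[(1/1.08 + 1/(1.08 × RR) + 2k)/359], held at its value for the observed RR
- Two-sided normal p-values

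Example with RR 0.70 and k = 3.22: SE = √[(0.926 + 1.323 + 6.44)/359] = 0.1556. Observed z = 0.3567/0.1556 = 2.29, p = 0.022. The shifted ratio is 0.85 × 0.70 + 0.15 = 0.745, so z = 0.2944/0.1556 = 1.89, p = 0.059.

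| Observed RR | k | p as observed | Shifted RR | p shifted |
|---|---|---|---|---|
| 0.60 | 0.5 | <0.001 | 0.66 | <0.001 |
| 0.60 | 1 | <0.001 | 0.66 | <0.001 |
| 0.60 | 2 | <0.001 | 0.66 | 0.002 |
| 0.60 | 3.22 | 0.001 | 0.66 | 0.008 |
| 0.70 | 1 | 0.001 | 0.745 | 0.007 |
| 0.70 | 2 | 0.007 | 0.745 | 0.026 |
| 0.70 | 3.22 | 0.022 | 0.745 | 0.059 |
| 0.75 | 2 | 0.028 | 0.788 | 0.068 |
| 0.80 | 0.5 | 0.016 | 0.83 | 0.044 |
| 0.80 | 1 | 0.036 | 0.83 | 0.081 |

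**Tipping point at the design effect.** With the SE recomputed at the shifted rate, significance at an observed 0.60 is lost only if the missing BFYS patients exacerbate at 1.64 per year (k = 3.22) to 2.34 per year (k = 0.5). That is 1.64/0.648 = 2.5 to 2.34/0.648 = 3.6 times the observed BFYS rate.

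**The case against.** The strongest reply is that only a journal article is shown, and the imputation model and its assumptions are commonly left to an analysis plan. The article never mentions missing at random. Multiple imputation is a framework, and control-based and delta-adjusted analyses are themselves multiple imputation, so the present wording is compatible with the remedy. This stands against the inference that the plan is committed to missing at random and cannot reveal a departure from it. It does not remove the point, because the article names this pair of methods in two sections, as its primary method and its check, and gives no rule that would make the check differ in assumption.

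A reader might also take the 15% as expected loss to follow-up. Section 2.4 offers it only as a dropout allowance. Continued follow-up off treatment, weekly diary review, monthly calls and quarterly home visits should keep missing outcomes below it. One of the three listed reasons for complete loss, relocation, need not concern health. Nothing shows that loss would differ between blinded arms.

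Nor do the figures support the inference that a result at the planned effect is fragile. The reversal at 0.70 needs k = 3.22; at k = 1 or 2 there is none.

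Loss at mid-year is milder. Only 7.5% of BFYS person-time is then unobserved, and the half-year that was observed belongs in the SE. With 360 full-year and 64 half-year patients per group and k = 3.22, an observed 0.72 has p = 0.024 and shifts to 0.925 × 0.72 + 0.075 = 0.741 with p = 0.039, still significant.

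**Conclusion.** The point holds in limited form. The named sensitivity analysis, in its standard form, does not vary the assumption on which the primary handling of missing data rests. Some of the loss is plausibly related to health.

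The practical effect depends on the result. At the planned rate ratio of 0.60 the conclusion survives for every k from 0.5 to 3.22. For weaker positive results near the significance boundary it can reverse, depending on k. This rests on an assumed dispersion, on 15% as an upper scenario with all loss at the start, and on reversion to the control rate in the BFYS arm only. The change is worth making, but the analysis is not invalid without it.

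**What to change.** In Section 2.9, state the assumption behind the planned multiple imputation and keep the standard version as the starting point. For the exacerbation count, add two analyses:

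- Control-based (reference) multiple imputation, in which unobserved time in the BFYS arm is imputed from the control rate.
- A delta-adjusted tipping-point analysis, which multiplies the imputed BFYS rate until significance is lost and reports that multiplier.

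The same edit should say how missing exacerbation time enters the Poisson or negative binomial model, since the mixed model for repeated measures is not the model named for the count. Section 2.3.4 should then refer to the revised text.

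The cost is wording and some programming. SAS 9.4, already used for the randomization, can run it if SPSS cannot. The sensitivity estimate will be less favourable than the standard one. Analysis is scheduled to begin in March 2027, so the change can be made before comparative results are seen, provided it also precedes the planned interim look.

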#### Inclusion criteria

2.3.2

Patients enrolled in this trial are required to meet the following criteria:

(1) Diagnosed with COPD in the stable phase.(2) With the frequent exacerbator phenotype of COPD.(3) Aged between 40 and 80 years.(4) With a stable disease condition for at least 4 weeks before enrollment.(5) Not having participated in other clinical trials within 1 month before enrollment.(6) Treated with dual bronchodilator or triple inhalation therapy for at least 3 months before enrollment.(7) Having undergone a 2-week washout period before enrollment.(8) Voluntarily participating in this trial and signing the informed consent form.

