#### Randomization and allocation

2.5.1

Randomization was performed using the block randomization method supervised by statisticians from the Good Clinical Practice (GCP) Center at the First Affiliated Hospital of Henan University of Chinese Medicine. The drug codes and randomization sequences were generated using SAS software (Version 9.4) and securely archived at the First Affiliated Hospital of Henan University of Chinese Medicine. Before the trial commenced, pre-prepared blinded drugs and corresponding emergency unblinding envelopes were allocated to each center by consecutive number segments. Drug dispensing at each center followed the ascending order of available numbers, with eligible participants receiving medications according to their enrollment order.

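### Continuous secondary outcomes are committed to methods not stated to adjust for baseline, and the count models name no centre or baseline terms; adding them would gain precision

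*Protocol article*

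**What the plan says.** **Continuous secondary outcomes.** Section 2.9 names repeated-measures ANOVA or, for non-normal data, the Friedman test. It adds Mauchly's test with the Greenhouse–Geisser correction, and LSD-t or Tamhane's T2 for comparisons between arms. Section 2.7.2 and Table 2 show lung function, symptom and sign scores, 6MWD, CAT and SF-36 measured at baseline and every 13 weeks.

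**Count outcomes.** For the primary outcome, section 2.9 says "For the primary outcome, Poisson regression or negative binomial regression will be used based on overdispersion tests"; secondary counts follow the same methods. No covariates are named. The only covariate in the section is time, in a mixed model for repeated measures that is meant for missing data and unequal follow-up.

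**Randomisation.** Section 2.4 says "Due to the centralized blocked randomization with block sizes of 4". Section 2.5.1 says that the blinded drugs and unblinding envelopes "were allocated to each center by consecutive number segments" and that each centre dispensed in ascending order.

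**Information at entry.** Section 2.3.2 requires "Treated with dual bronchodilator or triple inhalation therapy for at least 3 months before enrollment", so dual or triple therapy is known for everyone. The frequent-exacerbator phenotype is also required, but Table 2 lists only medical history and not a prior-year exacerbation count.

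**The concern.** For the continuous outcomes the article does not stop at a model family. It names the tests down to the post-hoc comparison. An LSD-t or T2 comparison at a visit has no baseline term, and Friedman accepts no covariate. If the analysis is run as described, information collected on every participant is left out, and chance differences between arms at baseline stay in the estimates.

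For the count outcomes, if exacerbation rates or case-finding differ between centres, a model without centre counts that variation as noise, although the allocation has already largely balanced it between arms. The standard error of the log rate ratio is then larger than it needs to be. Background therapy, and prior-year exacerbations where recorded, may also explain part of the dispersion.

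What is at stake is width of intervals and power, not the validity of the test.

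**Working it through.** **1. The plan's own figure.** Inputs from section 2.4: "the annual frequency of acute exacerbations in the control group was 1.08 episodes"; "the experimental group is expected to have a 40% reduction", hence 0.648 and a rate ratio of 0.60; alpha and power "of the hypothesis test were set at 0.05 and 0.9". Sidedness is not stated; two-sided is assumed.

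Formula: n per arm = (1.960 + 1.282)² × (1/λ₁ + 1/λ₂ + 2k) / (ln RR)², where k is the negative binomial dispersion.

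1/1.08 + 1/0.648 = 0.926 + 1.543 = 2.469.

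With k = 0 (Poisson) this gives 100 per arm. The article reports "The estimated sample size for each group was 359 participants using PASS software", which the formula reaches only with k of about 3.22 (about 4.23 if one-sided). The later steps reproduce: 359/0.85 gives 423, then 424 per arm and 848 in total. The article states no dispersion, so 3.22 serves below only as the value that 359 implies.

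**2. Continuous outcomes.** Let ρ be the correlation between baseline and follow-up, with equal variances. Relative to a post-value comparison, a change score has variance 2(1 − ρ) and baseline adjustment (ANCOVA) has 1 − ρ². So:

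- ANCOVA against post-value: 1 − ρ²
- ANCOVA against change score: (1 − ρ²) / [2(1 − ρ)] = (1 + ρ)/2

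| ρ (assumed) | against post-value | against change score |
|---|---|---|
| 0.6 | 0.64 | 0.80 |
| 0.7 | 0.51 | 0.85 |
| 0.8 | 0.36 | 0.90 |

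Both ratios are below 1 for any ρ strictly between 0 and 1, so the direction does not depend on the assumed values.

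**3. Primary outcome.** Suppose that centre and covariates remove a share of k (assumption). With 359 per arm and a rate ratio of 0.60:

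| share of k removed | power, k = 3.22 | n per arm for 90% power, k = 3.22 | power, k = 1 |
|---|---|---|---|
| 0% | 90.0% | about 359 | 99.6% |
| 5% | 91.0% | 347 | 99.6% |
| 10% | 92.0% | 334 | 99.7% |
| 20% | 93.9% | 308 | 99.8% |
| 30% | 95.6% | 282 | 99.9% |

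At 20% the variance ratio, unadjusted to adjusted, is (2.469 + 2k)/(2.469 + 1.6k): 1.098 at k = 1 and 1.169 at k = 3.22. With k = 0 there is no dispersion to remove. If the true rate ratio were 0.70 and k = 1, removing 30% would move power from 90.6% to 94.3%.

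**4. Simulation.** Negative binomial fits were run with and without centre and one covariate: 12 centres, 360 per arm, blocks of 4, 150 runs per setting. Assumed log-scale effects were a centre SD of 0.3 to 0.5 and a covariate effect of 0.3 to 0.4. The mean standard error of the log rate ratio fell by about 3 to 9% with adjustment (for example 0.150 to 0.145, and 0.120 to 0.110). Under no effect, rejection was 3.3 to 7.3% unadjusted and 4.0 to 7.3% adjusted. The simulation error is √(0.05 × 0.95/150), or about 1.8 percentage points, so neither differs detectably from 5%.

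**5. Balance within centre.** A centre holding consecutive numbers from a block-of-4 list can have at most its first and last blocks cut. Each cut block adds an imbalance of at most 2, so the arms differ by at most 4 at any centre.

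**The case against.** The strongest objection is that a covariate list belongs in the statistical analysis plan, which is not shown, and that a condensed article may leave it there. That stands for the count and logistic models. A reader might infer that the sponsor has chosen unadjusted models; the article does not say so, and the absence of covariates there is only silence. It carries less weight for the continuous outcomes, where the tests themselves are named.

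Second, baseline may enter the repeated-measures ANOVA as one of its time levels. The article does not say. If it does, the group-by-time contrast is a change-type comparison and the gain is 10 to 20% of the variance at ρ of 0.8 to 0.6. A reader might take the 36 to 64% reduction as the general gain; it applies only against a post-value comparison.

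Third, stratification by centre is never stated, and the list is called centralised. Exact balance by design would need segments in multiples of 4 and completed blocks. Near-balance needs neither, and it is enough for the precision argument.

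Fourth, a reader might suppose that strong predictors are already on file. No figure in the document supports strong. Exacerbation history is truncated at two or more by the phenotype definition in the Introduction, its count is not a listed baseline item, and section 2.6 ties triple therapy to exacerbation history, so the two may overlap.

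Finally, a reader might extend the precision claim to the logistic models. There adjustment can raise power but does not narrow the interval for the odds ratio.

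**Conclusion.** The point holds as a precision improvement; nothing in the plan is invalid, and the null simulations show no sign of an inflated error rate from leaving the terms out.

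It is firmest for the continuous secondary outcomes. The named methods are not stated to adjust for a baseline value that is collected on each outcome, and baseline adjustment is more efficient than either a post-value or a change-score comparison. The size depends on assumed correlations of 0.6 to 0.8 and on which of the two comparisons the ANOVA amounts to.

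For the primary and hospitalised-exacerbation counts the case is softer. The document gives no dispersion, no variation between centres and no covariate effects. The gain runs from about 1 to 6 points of power at the implied k of 3.22 to almost nothing at k of 1 or less with a rate ratio of 0.60. Including centre is reasonable because arms are nearly balanced within it.

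**What to change.** **Continuous outcomes.** Replace repeated-measures ANOVA, Friedman and the LSD-t/T2 comparisons with the mixed model for repeated measures that section 2.9 already names. Fit it to post-baseline visits with arm, visit, arm-by-visit, baseline value and centre.

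**Primary and hospitalised-AECOPD counts.** State the covariates, or confirm that the analysis plan does: centre (as a random effect, or with small centres pooled by a stated rule), background dual or triple therapy and, if the count is recorded, prior-year exacerbations. Report the unadjusted model as supportive.

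**Timing.** Fix the list before the interim efficacy and futility look described in section 2.8.2, not merely before final unblinding.

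**Cost.** Wording in the analysis plan and a rule for small centres. Baseline outcome values and inhaled therapy at entry are already part of the planned data; whether the prior-year count is recorded as a number needs checking against the case report form.
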